# ASSESSMENT OF THE IMPACT OF CLEANING METHODS AND OVERNIGHT DENTURE STORAGE ON BIOFILM FORMATION ON REMOVABLE ACRYLIC DENTURES.

**Aim of the study**

The presence of a biofilm – *i.e.* structured microbial communities that are attached to a surface and encased in an exopolymer matrix – on acrylic removable dentures has been associated with serious systemic conditions, especially in the dependent elderly [1]. Oral bacteria have been implicated in bacterial endocarditis [2], aspiration pneumonia [3, 4], chronic obstructive pulmonary disease [5, 6], amongst other diseases [1, 7]. Evidence is available regarding the relationship between proper oral hygiene and overall systemic health.

Plaque on dentures is a complex aggregate containing more than 108 organisms per milligram, and involving more than 600 prokaryote species [8]. The different species collaborate to form a symbiotic biofilm. The biofilms in dentate patients have been studied extensively, but there have been few studies on the biofilm microbiota of complete acrylic dentures [10-18]. It appears that distinct biofilms, with associated pathogenic risks, are present in ‘healthy’ *versus* denture stomatitis affected participants [15, 16, 18]. Not only poor denture cleaning but also inappropriate habits, such as wearing dentures overnight have proved to be associated with the prevalence of *Candida*-associated stomatitis [19, 20]. Therefore, the overnight removal of the acrylic removable dentures is advised in clinical settings. Although evidence-based guidelines for denture care and maintenance are available [21], guidelines for nocturnal storage conditions of dentures are missing. We therefore performed a study[[1]](#endnote-2) (*submitted for publication*) to evaluate the effect of different overnight storage protocols on denture biofilm formation and maturation. The results of this study showed that the use of cleansing tablets (Corega Tabs Anti-bacteria®, GlaxoSmithKline Consumer Healthcare SA, Genval, Belgium) for acrylic removable denture overnight storage reduces denture biofilm mass and pathogenicity compared to dry and water preservation.

As no mechanical denture cleaning was performed in the aforementioned study, the aim of the proposed study is to evaluate the combined effect of mechanical cleaning and overnight storage condition on the microbial composition and *Candida albicans* colonization of denture biofilm formation. This information is required to develop a clinical guideline on acrylic denture cleaning and overnight storage aiming to reduce the risk posed by pathogenic microorganisms, particularly in bedridden and immunocompromised patients.

**Research questions**

- What is the effect of mechanical cleaning on biofilm formation on removable acrylic dentures?
- Is ultrasonic cleaning more efficient compared to denture brushing with respect to prevention of biofilm formation on removable acrylic dentures?
- What is the effect of overnight storage in water with a cleansing tablet on biofilm formation on mechanically cleaned removable acrylic dentures?

**Materials & Methods**

- Participants
- number: 13
- Inclusion criteria:
  - Institutionalised frail elder
  - Fully edentulous in lower and upper jaw
  - Removable denture wearer in lower and upper jaw
  - Good oral health
- Exclusion criteria:
- Current or history of corticosteroid treatment within the 3 months prior to the study
- Current or history of antimicrobial treatment within the 3 months prior to the study
- Inability to provide informed consent
- Inability to comply with the study requirements
- Test conditions

|  | Denture cleaning method |  | Denture overnight storage condition |
| --- | --- | --- | --- |
| 1 | Brushing with water | B+T | Immersion in water with a cleansing tablet |
| 2 | Brushing with water | B | Immersion in water without a cleansing tablet |
| 3 | Ultrasonic cleaning | U+T | Immersion in water with a cleansing tablet |
| 4 | Ultrasonic cleaning | U | Immersion in water without a cleansing tablet |

- Study design
  - Cross-over study with randomized sequence of the 4 test conditions

This implies that all 4 test conditions will be executed within each of the 30 study participants.

- - The sequence of the test conditions for the individual participants will be randomized.
  - Double blind (both the participants as well as the investigators do not know the test conditions)
- All test conditions will be applied for 5 days. This means that all patients will undergo 4 test periods of 5 days.
- Each test period will be preceded by a wash-out period of 2 days in which the standard of care will be applied. This standard of care is denture cleaning through brushing with water and soap and overnight storage in water.
- All dentures will be decalcified using vinegar prior to the start of the study.
- At the start of the study, all dentures will be mechanically cleaned by means of denture brushing and additional ultrasonic cleaning. After mechanical cleaning, the dentures will also be desinfected using a 1% chlorhexidine digluconate gel (Corsodyl gel, GlaxoSmithKline Consumer Healthcare SA, Genval, Belgium).
- After mechanical denture cleaning and desinfection at the start of each test period, control samples (n=4) will be taken to evaluate the effectiveness of the cleaning and desinfection procedures.
- After each test period, test samples (n=4) will be taken
- The participants will be asked not to clean their dentures themselves. 2 care takers involved in the study will do the denture cleaning and will apply the appropriate overnight storage condition.
- Outcome measures:
  - - Clinical health of the denture bearing mucosa

*Method: clinical evaluation*

- - - Microbial analyses

*Method:* ***qualitative and quantitative PCR analyses for 20 selected oral bacteria*** *(Aa, Pg, Tf, Td, Pi, Fn, Pm, Pn, Cg, Cr, En, Ec, Cs, Cc, Sm, Sg, Sc, Ao, Av, Vp) and for* ***Candida Albicans.***

| Abbreviation | Genus & Species |
| --- | --- |
| *Aa* | *Aggregatibacter actinomycetemcomitans* |
| *Av* | *Actinomyces viscosus* |
| *Ao* | *Actinomyces odontolyticus* |
| *Cs* | *Capnocytophaga species* |
| *Cc* | *Campylobacter concisus* |
| *Cg* | *Campylobacter gracilis* |
| *Cr* | *Campylobacter rectus* |
| *Ec* | *Eikenella corrodens* |
| *En* | *Eubacterium nodatum* |
| *Fn* | *Fusobacterium nucleatum* |
| *Pg* | *Porphyromonas gingivalis* |
| *Pi* | *Prevotella intermedia* |
| *Pm* | *Peptostreptococcus micros* |
| *Pn* | *Prevotella nigrescens* |
| *Sc* | *Streptococcus constellatus* |
| *Sg* | *Streptococcus gordonii* |
| *Sm* | *Streptococcus mitis* |
| *Td* | *Treponema denticola* |
| *Tf* | *Tannerella forsythensis* |
| *Vp* | *Veillonella parvula* |

Biofilm sampling will be performed in a 5-mm diameter circular region of interest, situated bucco-distally to the lower second premolars (Figure 1). In order to standardize the position and dimensions of this region and to ensure optimal reproducibility of the microbial sampling, a custom-made mold of each lower prosthesis with PPSU (Polyfenylsulfon) placeholder rings will be made (Optosil®, Heraeus Kulzer GmbH, Hanau, Germany) (Figure 1). The placeholder rings will be placed in such a way that the transition between artificial teeth and gums is situated centrally. These molds will fabricated following denture disinfection at the start of the study, and will be re-used throughout the study because of the absence of dimensional changes over time when preserved properly (*i.e.* dry and in plastic bag). The molds will be disinfected and the rings will be ultrasonically cleaned and sterilized after each microbial sampling.

- - - Denture plaque score

*Method: Denture plaque will be scored after microbial sampling, independently by 2 investigators using 4% erythrosine disclosing solution according to Augsburger and Elahi [22] (score range 0-4)*

- Study protocol

| Time point | Action | Microbial sampling |
| --- | --- | --- |
| Day 0 (morning) | Calculus removal using vinegar  Mechanical denture cleaning ° |  |
| Day 0-2 | Standard of carei |  |
| Day 3 (morning) | Mechanical denture cleaning° and desinfectionii | control sample 1* |
| Day 3-7 | Test period 1 |  |
| Day 7 (evening) | Mechanical denture cleaning° and desinfectionii | test sample 1** |
| Day 8-9 | Standard of carei (wash-out period) |  |
| Day 10 (morning) | Mechanical denture cleaning° and desinfectionii | control sample 2* |
| Day 10-14 | Test period 2 |  |
| Day 14 (evening) | Mechanical denture cleaning° and desinfectionii | test sample 2** |
| Day 15-16 | Standard of carei (wash-out period) |  |
| Day 17 (morning) | Mechanical denture cleaning° and desinfectionii | control 3* |
| Day 17-21 | Test period 3 |  |
| Day 21 (evening) | Mechanical denture cleaning° and desinfectionii | test sample 3** |
| Day 22-23 | Standard of carei (wash-out period) |  |
| Day 24 (morning) | Mechanical denture cleaning° and desinfectionii | control 4* |
| Day 24-28 | Test period 4 |  |
| Day 28 (evening) | Mechanical denture cleaning° and desinfectionii  END OF THE STUDY | test sample 4** |

°mechanical denture cleaning: brushing with water and soap + additional ultrasonic cleaning

i standard of care: denture brushing with water and soap and overnight storage in tab water

iidesinfection with 1% chlorhexidine digluconate gel (Corsodyl gel, GlaxoSmithKline Consumer Healthcare SA, Genval, Belgium)

*control sampling: after mechanical cleaning and desinfection

**test sampling: before mechanical cleaning desinfection

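### The protocol states two incompatible trial sizes for the same cross-over, 13 participants and 30 participants, and nothing in it reconciles them.

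*Protocol*

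**What the plan says.** All the relevant text is in the protocol, section Materials & Methods.

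- **Participants item.** The number of participants is given as 13, directly above the eligibility criteria.
- **Study design item.** The design is described as a "Cross-over study with randomized sequence of the 4 test conditions". The next sentence reads: "This implies that all 4 test conditions will be executed within each of the 30 study participants".
- **Same item, duration.** After fixing each condition at 5 days, the protocol adds: "This means that all patients will undergo 4 test periods of 5 days".
- **Same item, sampling.** "After each test period, test samples (n=4) will be taken". The day-by-day table under Study protocol shows one control sample and one test sample in each of the four periods.

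The document does not mention a screening number, a dropout allowance, a subgroup or a second cohort. The sponsor's earlier storage study is described in Aim of the study without a participant number.

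**The concern.** The number of participants is the first figure a reader takes from a trial plan. Here it decides how many frail institutionalised elders are enrolled, how many custom molds are made (one per lower prosthesis) and how many samples go to PCR. In a complete cross-over it also sets the standard error of every comparison between conditions.

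One of the research questions is whether ultrasonic cleaning is more efficient than brushing, and the results are meant to inform a clinical guideline. An inconclusive answer from 13 people carries less information than one from 30. As written, two readers of the same section can take away trial sizes that differ more than twofold.

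**Working it through.** **1. Can the two numbers describe different things?** Each possible reading was checked against the text.

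- *Screened versus enrolled, or an attrition allowance.* The Study design sentence has the conditions carried out in every one of the 30, and the protocol says that all patients go through all four periods. Going from 30 to 13 would need a loss of 1 − 13/30 = 0.567, or 57%, and no loss is mentioned.
- *Subgroup.* None is defined.
- *Dentures or samples versus persons.* The sentence counts participants. The count attached to samples is 4.
- *The earlier study.* The sentence with 30 concerns the four conditions of this trial.

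No reading reconciles them.

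**2. Can either number be reproduced?** No. The protocol gives no significance level, power, effect size, standard deviation or dropout rate. Those may stand in a statistical analysis plan that is not at hand, so their absence is not counted here. It does mean that the document offers no calculation from which to tell which number is intended.

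**3. Difference in size.**

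- Participants: 30/13 = 2.31.
- Test samples, at one per participant per period over four periods: 13 × 4 = 52 against 30 × 4 = 120.

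**4. Difference in standard error.** For a within-participant contrast in which every participant receives every condition, SE = SD_diff/sqrt(N).

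- N = 13: SE = SD_diff/sqrt(13) = 0.277 SD_diff.
- N = 30: SE = SD_diff/sqrt(30) = 0.183 SD_diff.
- Ratio: sqrt(30/13) = 1.52.

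The unknown SD cancels, so the ratio needs no outside input.

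**5. Illustration only.** The figures below assume a two-sided test, 80% power and a continuous outcome. None of these is stated in the protocol.

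| Assumed analysis | N = 13 | N = 30 |
| --- | --- | --- |
| Additive participant/period/condition model, residual df 3(N−1)−3 = 33 and 84, 5% level: detectable factorial main effect, in residual SD | 0.80 | 0.52 |
| Same model, one pair of conditions, in residual SD | 1.13 | 0.73 |
| Same model, main effect, level 5%/21 (20 bacteria plus *Candida*), in residual SD | 1.16 | 0.73 |
| Plain paired t-test, one pair, 5% level, in SD of the difference | 0.85 | 0.53 |

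The main-effect formula uses SE = s/sqrt(N) and the pairwise formula uses SE = s·sqrt(2/N), where s is the residual SD. Both treat the conditions as balanced over periods. Under the 5% additive model, the main effect of 0.52 residual SD that 30 participants would detect with 80% power has about 44% power with 13. The spread between rows shows how far the absolute figures depend on the assumed analysis.

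**The case against.** The strongest reply is that this is a drafting slip with no consequence. The 13 stands in the item meant for the number of participants. The 30 appears in an explanatory aside whose purpose is to say that each person receives all four conditions, which holds at either size. A slip is plausible, but the document does not prove it, and a reader could as well suppose that the Participants line is the one in error. The contradiction therefore stands whatever its origin.

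Other objections limit what may be built on it, and they succeed.

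- **Planned precision.** A reader might infer that the two numbers leave the trial's planned precision undefined. The protocol plans no precision, since it states no level, power, SD or effect. What is undefined is N.
- **Detectable effects.** A reader might take 0.80 against 0.52 SD as the size of the problem. Those values rest on an analysis that the protocol does not state. They treat one continuous outcome with one test, whereas the outcomes include qualitative PCR, a clinical evaluation of the mucosa, a plaque score from 0 to 4, and 21 organisms. Neither 13 nor 30 is divisible by 4, so exact balance of conditions over periods is impossible at either size and the formulas are approximate.
- **Early termination.** A reader might infer that stopping at 13 would look like an early stop against a target of 30. The protocol has no recruitment or stopping rule on which to base that, and nothing shows that anyone relied on 30.
- **Missing justification.** A statement of the detectable effect is commonly left to the statistical analysis plan, so its absence from the protocol is not an error.

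**Conclusion.** The protocol is wrong as written: it gives two trial sizes for one cross-over population, and at least one must be incorrect. This is an internal contradiction in sample size, not an error of arithmetic.

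Its size is a factor of 2.31 in participants and 1.52 in the standard error of any within-participant contrast. The second figure assumes only complete data and the same SD at both sizes. The count of 52 against 120 test samples further assumes one test sample per participant per period, as the day-by-day table shows.

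The need to correct it rests on the contradiction alone. The power and detectable-effect figures illustrate the difference under stated assumptions and carry no weight in the conclusion. The document does not show which number is right, and this review does not choose one.

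**What to change.** The sponsor should state the one intended number of participants and use it in both the Participants and the Study design items. If 13 is intended, 30 becomes 13 in the Study design sentence. If 30 is intended, 13 becomes 30 in the Participants item. Any other document that quotes the trial size should be checked against the corrected figure.

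The cost is a one-line correction. If 13 is kept, the stated size is the less favourable of the two. No detectable-effect figure from this review should be inserted in the protocol, because all of them depend on assumptions that the sponsor has not made there.
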